### Randomization

Matched pairs of coalitions will be randomly assigned to the Coalition Check-Up condition or TA as usual. Coalitions will be matched on level of TA availability at baseline (0 = none, 1 = occasional trainings and group TA, 2 = regularly scheduled group TA, 3 = group TA and regularly scheduled one-on-one supervision, 4 = regularly scheduled one-on-one capacity-building TA), years in operation, coalition model employed, population density, US Census poverty rate, and availability of funding. A random number seed will be generated by an external third party using random.org. SAS Proc Surveyselect uses this random number seed to select one of each pair of coalitions recruited into the study as the intervention condition. Data collectors and data analysts will be blind to study condition, with no circumstances under which unblinding is permissible.

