### Intervention implementation monitoring

Dimensions of Coalition Check-Up implementation quality include (1) coalition-TA provider collaborative working relationship, (2) action plan quality and implementation, and (3) fidelity to the Coalition Check-Up model. The collaborative working relationship between the TA provider and coalition leader/coalition will be assessed with measures drawn from [name], [name], and [name]’s prior work on PROSPER [13, 43, 44]. The scale captures trust between the TA provider and the coalition, empowerment vs. providing information-only, and mutual respect. Collaborative working relationship will be assessed quarterly by TA providers and rated annually via the coalition leader interview. Developing a collaborative working relationship is a foundational principle in motivational interviewing.

Ratings of action plan quality and implementation will employ measures developed previously by the research team [45, 46]. As in prior studies, investigators will create a scoring rubric and test it on existing coalition implementation plans external to the randomized trial. Then inter-rater reliability will be calculated, with a minimum of 30% of the implementation plans independently rated by two members of the research team [47].

Coalition Check-Up fidelity will be assessed with three measures: (1) the TA Record completed by TA providers after monthly coalition contacts, (2) the coalition leader interview, and (3) expert ratings of motivational interviewing fidelity. Through the TA Record, we will know whether the TA provider is contacting coalitions monthly and spending adequate amounts of time on each Coalition Check-Up step. The coalition coordinator interview provides a more objective perspective on Coalition Check-Up fidelity, assessing the extent to which coalitions complete each Coalition Check-Up step. Assessment of TA provider motivational interviewing fidelity relies on motivational interviewing experts coding recordings of TA sessions, noting desired and undesired motivational interviewing behaviors using Motivational Interviewing Treatment Integrity codes [48, 49]. All TA sessions will be recorded and 10% will be coded. A motivational interviewing expert will use the codes to give TA providers feedback and coaching as needed to ensure their work remains consistent with motivational interviewing principles [50].

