#### Aim 2: Data collection—EBP implementation

We will annually interview coalition leaders on the coalition’s role in coordinating and sponsoring EBPs, and EBP coordinators on the EBP implementation measures—each receives $20 compensation for each interview [51]. To minimize bias, our measures of EBP implementation rely on factual information about program implementation asked in a standardized fashion across programs—such as the involvement of certified trainers, fidelity monitoring, and program adherence.

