### Data management and monitoring

We will use RedCap, a secure platform for online surveys and telephone interview data entry. RedCap minimizes data entry errors because survey respondents and interviewers use the interface to directly enter data. All data collection protocols include a form on which research staff members record any problems with the data collection or adverse events. Once data entry is complete, the data is exported to SAS, where all data manipulations are automatically documented in the process of writing SAS code.

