#### Aim 2: Measures—EBP implementation

EBP implementation consists of three core facets assessed annually: (a) quantity. (b) quality, and (c) sustainability. EBP quantity is a coalition-level variable computed as the number of youth reached annually by all coalition-supported EBPs. To estimate the total number of youth reached by a particular EBP, we ask the coordinator of the EBP to report the unduplicated number of youth reached annually at each location where the program is being implemented. Thus, EBP quantity represents the sum “reach” achieved by complementary programs implemented by a coalition to address different developmental stages across the prevention spectrum.

EBP quality is a coordinator-reported program-level variable computed as a composite of 7 scales: (a) staff training (6 items, α = .91); (b) staff motivation and competence (5 items, α = .93); (c) fidelity monitoring (11 items, α = .76); (d) evaluation (13 items, α = .81); (e) dosage (2 items); (f) adherence (7 items); and (g) implementation barriers (11 items, α = .81) (21, 26).

EBP sustainability consists of two measures: (1) overall EBP sustainability and (2) sustainability planning. Overall EBP sustainability is a coalition-level variable that is the sum number of years all EBPs are in operation during years 2–4 of the project, including both existing and new EBPs. An EBP will be designated as non-operational when (a) it has no reach or (b) there is an absence of ongoing training or TA in the past 12 months and no funding available to support the program. Sustainability planning is a coordinator-reported program level outcome (12 items, α =.85) [57].

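### The no-exception blind for data collectors and analysts conflicts with a coalition leader interview that asks about completion of each Check-Up step, and with the planned process analyses

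*Protocol article*

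**What the plan says.** The Randomization section sets an absolute rule: "Data collectors and data analysts will be blind to study condition, with no circumstances under which unblinding is permissible".

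The section on intervention implementation monitoring says that Check-Up "fidelity will be assessed with three measures: (1) the TA Record completed by TA providers after monthly coalition contacts, (2) the coalition leader interview", with expert ratings of motivational interviewing as the third measure. It then explains the purpose of the interview: "The coalition coordinator interview provides a more objective perspective on Coalition Check-Up fidelity, assessing the extent to which coalitions complete each Coalition Check-Up step". The list of measures names the leader and the explanation names the coalition coordinator; I read these as the same interview. The same section adds: "Collaborative working relationship will be assessed quarterly by TA providers and rated annually via the coalition leader interview".

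The Aim 2 data collection section also relies on a leader interview, alongside a separate one with programme coordinators: "We will annually interview coalition leaders on the coalition’s role in coordinating and sponsoring EBPs, and EBP coordinators on the EBP implementation measures". On data entry, the data management section says: "RedCap minimizes data entry errors because survey respondents and interviewers use the interface to directly enter data".

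**The concern.** A blinding statement tells readers how far they can trust outcome data against detection bias. Here nothing suggests that respondents are unaware of their own arm, so the state of knowledge of the person asking and recording is a protection that readers will count on. The article claims that protection without exception, while one of its own instruments asks about something that largely exists in one arm only.

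Two things are at stake. The trial would report a blinding property that its procedures defeat. In addition, probing or recording of the leader's answers on the coalition's part in coordinating and sponsoring programmes could differ by arm, because that topic is also assigned to a leader interview.

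**Working it through.** No formula applies to the conflict itself, so the check sets the sections side by side.

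**1. What differs between arms.** The opening of the Method section says that all coalitions complete the annual assessment and receive a report, and that both arms keep usual technical assistance (TA). Personalized outreach goes to the Check-Up arm alone. The step descriptions under Intervention procedures show that this outreach delivers step 2 (joint review of findings), step 3 (action plan) and step 4 (support while the plan is carried out). Step 1 is common to both arms; steps 2 to 4 are not.

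**2. What the interview asks.** It is described as "assessing the extent to which coalitions complete each Coalition Check-Up step". If the items are put to one arm only, the script reveals the arm. If they are put to both, the answers on steps 2 to 4 reveal it. Interviewers key in answers themselves, so they cannot avoid seeing them.

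**3. Does staffing rescue the rule?** No. A separate interviewer for fidelity items is still a data collector, and the rule allows no exception. It fails for whoever conducts this interview, from the first round after a cycle.

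**4. Which Aim 2 data are touched.**
- *Directly:* the leader interview, which Aim 2 uses for the coalition's role in coordinating and sponsoring programmes. By inference only, it may also help settle which programmes count as coalition-supported, and so which enter the sums for quantity and overall sustainability.
- *Conditionally:* reach, quality and sustainability planning. The Aim 2 measures section takes reach from the programme's own coordinator ("we ask the coordinator of the EBP to report the unduplicated number of youth reached annually") and labels quality and sustainability planning as coordinator-reported. Those interviews are not described as containing any Check-Up item. They lose the blind only if the same staff conduct both kinds of interview.
- *Not touched:* the Aim 1 web survey of members and the Aim 3 state youth surveys.

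**5. Which analysts are touched.** The conceptual framework section plans moderation tests on motivational interviewing fidelity and working relationship, and mediation tests on action plan quality and implementation. Motivational interviewing fidelity is coded from recorded TA sessions, and action plans are produced in step 3. Both are described only as part of the Check-Up, so an analyst who links them to coalitions can infer the arm. The main Aim 1–3 effect models do not take these data as inputs. Their 0/1 condition code specifies a model and is compatible with masked labels.

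**6. Count of exposed interviews.** Inputs: 68 coalitions (Coalition recruitment) and three annual cycles (Intervention procedures). Assuming one leader interview per coalition in each of three follow-up rounds, 68 × 3 = 204. This counts leader interviews, not programme coordinator interviews.

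**The case against.** The strongest reply is that this is a wording problem in a condensed article. Who conducts which interview, in what order, and whether the two uses of the leader interview form one session are details that a full protocol commonly holds. The article separates fidelity monitoring from Aim 2 data collection by section and, for reach, quality and sustainability planning, by respondent. It also names its own protection for Aim 2: factual items asked in the same way across programmes.

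Much of that stands. A reader might infer that all Aim 2 interviews are unblinded; the documents do not support this, because the implementation measures come from programme coordinators and no overlap of staff is stated. A reader might also infer that the working-relationship rating gives the arm away. It need not: both arms have usual TA, and the matching scale for baseline TA runs up to regular one-on-one support, so control leaders may also have a provider to rate. Nor does it follow that outcome analysts must be unblinded.

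What does not stand is the idea that unstated staffing detail could make the rule true. The rule covers every data collector, and one of them must hear or record the step-completion answers. Standardized factual items limit the effect of knowing the arm but do not restore the blind.

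**Conclusion.** The conflict is real and narrow. The no-exception blind does not hold for the person conducting the coalition leader or coordinator interview, or for analysts of the motivational interviewing and action plan data. This rests only on the stated interview content and on outreach being confined to one arm.

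Exposure of Aim 2 content rests on a further assumption: that the fidelity items and the programme-role items are asked in one session or by the same staff. That is a reasonable reading, but the article does not say it. Exposure of reach, quality and sustainability planning needs a second assumption, that leader interviewers also interview programme coordinators.

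The scale is up to 204 leader interviews on the count above. No size of bias can be derived from the document, and none is claimed. The point deserves correction because readers will rely on the statement and the remedy is cheap; it does not show that the Aim 2 results would be biased.

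**What to change.** 1. Take the step-completion items out of any interview conducted by outcome data collectors. Collect them by a RedCap web form that the leader completes, with responses withheld from those interviewers in every round. Moving the items to the end of the interview is not enough, because the same interviewer would know the arm in later rounds.

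2. Use masked arm labels for the Aim 1–3 effect models. Link fidelity and action plan data only after those models are final.

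3. Restate the Randomization sentence so that blinding covers outcome data collectors and outcome analysts until the outcome models are final, and say that coalitions, TA providers, fidelity raters and process analysts are not blind.

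Cost: one short extra web form per leader per year, a masked arm variable, a wording change, and fidelity analyses that wait for the outcome models. No additional interviews are needed.

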### Intervention procedures

The Coalition Check-Up cycle will be repeated annually, a total of three times over 3 years. Consistent with previous coalition research suggesting it takes 2–3 years to detect an effect on youth substance use, we expect three Coalition Check-Up iterations will enhance coalition capacity and EBP implementation sufficiently to detect an effect on youth substance use [40, 41].

#### Coalition Check-Up Step 1: Assess coalition capacity and EBP implementation

All coalition members will be invited to complete an assessment of coalition capacity, and program coordinators will be asked to complete an assessment of EBP implementation. A researcher then uses these data to produce accessible feedback reports that visually display findings and support coalition-driven decision-making regarding what to improve.

#### Coalition Check-Up Step 2: Review findings

In this step, the TA provider jointly reviews the coalition profile with coalition leaders and members. The TA provider facilitates the discussion, presenting the results and specific questions for reflection at key points to encourage understanding and critical thinking while celebrating strengths and identifying areas for growth.

#### Coalition Check-Up Step 3: Develop action plan

Approximately 1 month after reviewing findings in step 2, the TA provider meets with the coalition again. After a brief review of the previously identified strengths and areas for growth, TA providers can facilitate large-group discussion on the top one, two, or three priorities, or divide the coalition into smaller groups, asking each to focus on an identified area for growth. Within each discussion, participants specify an improvement goal, use the Coalition Check-Up guidebook to brainstorm and select activities to reach their goal, and delegate members and committees to lead the work. At discussion’s end, each coalition officially adopts the action plan. The coalition leaders distribute the action plan with the meeting notes.

#### Coalition Check-Up Step 4: Action plan implementation

Once the action plan notes are distributed, action plan implementation monitoring and support begin. Coalition leaders check-in with members on progress, with updates at each coalition meeting. TA providers schedule two in-person visits at coalition meetings over the next 6 months to provide assistance, suggestions, resources, and feedback. Between in-person visits, the TA provider will check in with coalition leaders at least monthly. These regular check-ins are typically short (e.g., 30–60 min) but allow for continued relationship building using motivational interviewing techniques, information sharing, problem-solving, and other prompt support [42]. Our previous research suggests monthly TA provider contact enhances coalition program implementation and sustainability [15].

### Intervention implementation monitoring

Dimensions of Coalition Check-Up implementation quality include (1) coalition-TA provider collaborative working relationship, (2) action plan quality and implementation, and (3) fidelity to the Coalition Check-Up model. The collaborative working relationship between the TA provider and coalition leader/coalition will be assessed with measures drawn from [name], [name], and [name]’s prior work on PROSPER [13, 43, 44]. The scale captures trust between the TA provider and the coalition, empowerment vs. providing information-only, and mutual respect. Collaborative working relationship will be assessed quarterly by TA providers and rated annually via the coalition leader interview. Developing a collaborative working relationship is a foundational principle in motivational interviewing.

Ratings of action plan quality and implementation will employ measures developed previously by the research team [45, 46]. As in prior studies, investigators will create a scoring rubric and test it on existing coalition implementation plans external to the randomized trial. Then inter-rater reliability will be calculated, with a minimum of 30% of the implementation plans independently rated by two members of the research team [47].

Coalition Check-Up fidelity will be assessed with three measures: (1) the TA Record completed by TA providers after monthly coalition contacts, (2) the coalition leader interview, and (3) expert ratings of motivational interviewing fidelity. Through the TA Record, we will know whether the TA provider is contacting coalitions monthly and spending adequate amounts of time on each Coalition Check-Up step. The coalition coordinator interview provides a more objective perspective on Coalition Check-Up fidelity, assessing the extent to which coalitions complete each Coalition Check-Up step. Assessment of TA provider motivational interviewing fidelity relies on motivational interviewing experts coding recordings of TA sessions, noting desired and undesired motivational interviewing behaviors using Motivational Interviewing Treatment Integrity codes [48, 49]. All TA sessions will be recorded and 10% will be coded. A motivational interviewing expert will use the codes to give TA providers feedback and coaching as needed to ensure their work remains consistent with motivational interviewing principles [50].

### Data collection

#### Aim 1: Data collection—coalition capacity

Annually for 4 years, each member of a participating coalition will be invited to participate in a 20-min web-based coalition member survey, and each coalition coordinator will be asked to report on coalition operations and complete an implementation monitoring tool for community collaborations, modeled after the PROSPER and Communities That Care Milestones & Benchmarks tools. After working with the coalitions and their TA providers to obtain a coalition membership roster, the coalition leader notifies coalition members via email, announcements at meetings, and phone calls, about the survey and to convey support for participation. After the coalition leader notifies coalition members about the survey, data collection staff send the first survey invitation through email (or US mail if individuals do not use email). All respondents in intervention and control conditions receive $10 for completing each survey and their coalition receives a de-identified feedback report for strategic planning. Respondents receive up to four reminders to complete the coalition functioning survey, one per week. Finally, we call participants who have not completed the survey to troubleshoot any problems they may be having and encourage their participation.

#### Aim 2: Data collection—EBP implementation

We will annually interview coalition leaders on the coalition’s role in coordinating and sponsoring EBPs, and EBP coordinators on the EBP implementation measures—each receives $20 compensation for each interview [51]. To minimize bias, our measures of EBP implementation rely on factual information about program implementation asked in a standardized fashion across programs—such as the involvement of certified trainers, fidelity monitoring, and program adherence.

#### Aim 3: Data collection—youth substance use

We will measure youth substance use and related behaviors with the Pennsylvania Youth Survey and the Missouri Student Survey—statewide surveys similar to the Communities That Care Youth Survey [52]. In 2019, 413 out of 500 (83%) school districts in Pennsylvania participated, and in 2018, 102 of 115 (89%) counties participated in Missouri [53, 54]. The surveys are conducted free of charge in all schools in Pennsylvania and Missouri by their state governments. Survey data are collected every other year in 6th, 8th, 10th, and 12th grades. All instruments are available from the first author.

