#### Aim 3: Analyses

The final aim will be to test the hypothesis that communities receiving the Coalition Check-Up will reduce youth substance use relative to communities in the “TA-as-usual” condition. Youth reports of substance use will be nested in school district (i.e., community or coalition level) via multilevel models. We will start by testing for differences in baseline levels of youth substance use between the two experimental conditions, to examine balance after randomization. If these comparisons identify a difference between the two conditions on a particular measure, it will be included as a covariate in the modeling. Then, youth substance use outcomes in year 3 will be predicted by experimental condition. A longer-term analysis of the Coalition Check-Up’s impact on youth substance use becomes possible with year 5 outcome data. These longer term outcomes will capture the effect of the Coalition Check-Up delivered as a continuous quality improvement cycle over years 2–4 of the study. We will use the same analytic models in year 5 as year 3, given that the data is identifiable at the school-district level but not the student-level.

We will examine 8 youth substance use outcomes (see the “Aim 3: Measures—youth substance use” section) in two multivariate multi-level models [62]. The first model will test past 30-day use of alcohol, tobacco, marijuana, and opioids simultaneously within the coalition’s catchment area [62]. The second model will test lifetime usage outcomes of the same substances. If an overall significant effect is found for the Coalition Check-Up in a particular multivariate model, follow-up tests will examine the specific substances as separate dependent variables [62]. These models extend analyses of Pennsylvania Youth Survey data conducted by [name] and [name] by taking advantage of increased levels of survey participation, the availability of community-level pretest measures of youth substance use, and the collection of detailed EBP implementation data [24, 59, 65].

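### Aim 3 pools Pennsylvania and Missouri at a common year 3 and year 5, but the two state surveys run in alternating calendar years and the model has no state term

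*Protocol article*

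**What the plan says.** All references are to the protocol article.

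- **Data source** (Aim 3: Data collection—youth substance use). Outcomes come from the Pennsylvania Youth Survey and the Missouri Student Survey. Coverage is given as "In 2019, 413 out of 500 (83%) school districts in Pennsylvania participated, and in 2018, 102 of 115 (89%) counties participated in Missouri". On frequency: "Survey data are collected every other year in 6th, 8th, 10th, and 12th grades".
- **Time points** (Aim 3: Analyses). "Then, youth substance use outcomes in year 3 will be predicted by experimental condition". For the later analysis: "We will use the same analytic models in year 5 as year 3". The section places the intervention in study years 2 to 4.
- **Covariates** (Aim 3: Analyses). Baseline youth substance use is compared between conditions, and a measure that differs becomes a covariate. No other covariate is named for Aim 3.
- **Matching** (Randomization). Pairs are matched on baseline level of TA availability and on "years in operation, coalition model employed, population density, US Census poverty rate, and availability of funding". State is not listed.
- **Sample and dose** (Coalition recruitment; Intervention procedures). 68 coalitions are drawn from the two states, with no split given. The Check-Up cycle is annual and is run three times.

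**The concern.** The article fixes one early and one late outcome time for both states, while its own figures put the two surveys in opposite calendar years. It does not say which wave in each state serves as baseline, year 3 or year 5.

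Two things follow. First, outcomes labelled year 3 may reflect different amounts of intervention in the two states, so it is unclear what the pooled effect estimates. Second, differences between the states in outcome level, from the survey, the calendar year or the population, enter the treatment contrast unadjusted. Neither the matching list nor the covariate rule is certain to remove them. If waves are chosen once outcome data are in hand, that choice is also an avoidable analyst freedom.

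**Working it through.** **1. The stated coverage figures.** 413/500 = 82.6%, printed as 83%. 102/115 = 88.7%, printed as 89%. Both reproduce. What matters here is the survey years: 2019 for Pennsylvania, 2018 for Missouri.

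**2. Alternation.** With a two-year interval, Pennsylvania falls in 2019 + 2k (odd years) and Missouri in 2018 + 2k (even years). Years 3 and 5 are two years apart, so a biennial survey held in the same month each time is either in both study years or in neither.

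**3. Which surveys fall in years 3 and 5.** The article gives no start date and no survey months, so I enumerated them: four consecutive start years, 12 start months, and 12 possible survey months for each state.

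| Study year starts in | Pennsylvania only | Missouri only | Both | Neither | Total |
|---|---|---|---|---|---|
| January | 288 | 288 | 0 | 0 | 4 × 1 × 144 = 576 |
| Any other month | 2024 | 2024 | 1144 | 1144 | 4 × 11 × 144 = 6336 |

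These counts are not probabilities; they show what is possible. If study years are calendar years, exactly one state is surveyed in years 3 and 5. If a study year crosses a January, it can contain one survey, both or neither. For example, a year from autumn to summer can hold an odd-year autumn Pennsylvania wave and the next even-year spring Missouri wave.

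**4. How far apart the waves can be.** For any wave in one state, the two adjacent waves in the other are 24 months apart. The nearer one is therefore at most 12 months away.

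**5. Difference in exposure.** Assume that the three cycles fill study years 2, 3 and 4 evenly. Cycles completed at t years from study start are then min(3, max(0, t − 1)).

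| Survey falls in | t | Cycles completed |
|---|---|---|
| Year 2 | 1 to 2 | 0 to 1 |
| Year 3 | 2 to 3 | 1 to 2 |
| Year 4 | 3 to 4 | 2 to 3 |
| Year 5 | 4 to 5 | 3 |
| Year 6 | 5 to 6 | 3 |

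A wave one year away from year 3, in either direction, differs by one cycle of three, or 33% of planned exposure. For the final outcome, an off-year wave in year 6 differs by nothing, and one in year 4 by up to one cycle.

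**6. What cross-state pairs would do.** There are 68/2 = 34 pairs. Suppose c of them straddle the states and the states differ by D in outcome level (neither is given). Within such a pair, randomisation adds +D or −D to the treatment difference with equal probability. Averaged over 34 equally weighted pairs, the contribution has mean 0 and standard deviation D × √c / 34. This runs from 0 (c = 0) to D/√34 = 0.17 D (c = 34, every pair straddling). The contribution is noise with expectation zero.

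**The case against.** The strongest reply is that assigning survey waves to time points is operational detail which a condensed article leaves to the full protocol or SAP, neither of which is shown. For the wave assignment taken alone, that largely stands. It stands less well for the model: the article states the Aim 3 predictor and its covariate rule, and state is in neither.

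The reply is also right about several stronger readings that a reader might infer:

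- *One state has no survey at either time point, whatever the start date.* This follows if study years are calendar years. The article does not say so, and a study year crossing a January can hold both surveys.
- *The pooled model cannot be run.* Nothing prevents each state from contributing its own baseline and outcome waves.
- *Survey and calendar year are confounded with condition.* Condition is randomised within pairs, so a cross-state pair adds variance and possible chance imbalance, not systematic bias. The article does not report that any such pair exists.
- *A state drops out and the detectable effect of .25 grows.* No passage plans to drop a state and no split is given, so any figure would rest on two unstated premises.

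The rule of adjusting for measures that differ at baseline gives partial protection, but it reacts to substance use measures, not to state.

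**Conclusion.** The point holds as an inexpensive improvement, not as a contradiction that blocks the analysis. By the article's own figures the surveys alternate by calendar year, yet Aim 3 pools both states at a common year 3 and year 5 with no state term and no matching on state.

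If waves are a year apart, the early outcome could differ between states by up to about one of the three annual cycles; by the final wave the difference may be nil. This assumes that the cycles fill study years 2 to 4 evenly. The effect on precision cannot be quantified, because the state split, the number of cross-state pairs and the difference in outcome level between states are not given.

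**What to change.** In Aim 3: Analyses, include state as a fixed effect in every Aim 3 model at both time points, whatever the baseline tests show. The treatment effect then becomes a within-state contrast, and differences in outcome level between the states no longer enter it. The term cannot make effects measured at different exposure equal, so the timing has to be stated as well.

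Alongside it, name for each state the survey wave that serves as baseline (the last wave before randomisation), as early outcome and as final outcome. Fix these before outcome data are seen, and report months of exposure at each. Matching any pairs not yet formed within state is optional.

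The cost is one parameter among 68 clusters (with condition alone, 68 − 2 = 66 coalition-level degrees of freedom become 65) and a few lines of text. No new data are needed. Matching within state would slightly narrow the pool of possible partners.
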